### Interventions

#### Standard Treatment

Although there is variation in the content of each treatment program, they all adopt a similar biopsychosocial perspective on pain management [6,32]. Furthermore, each program includes (cognitive) behavioral treatment modalities (eg, graded activity, exposure in vivo, acceptance, and commitment therapy) as well as pain neuroscience education, active patient involvement, and structured team meetings to coordinate treatment and evaluate each patient’s progress. All programs are supervised by a physician in rehabilitation medicine who is responsible for patient screening, assessment, and monitoring of overall progress. The treatment team always includes a psychologist and a physical therapist or occupational therapist. At each location, patients start with pain education, where a biopsychosocial orientation toward pain will be explained. Patients also receive a manual that provides general information about the treatment program. All therapies are delivered at the location of the treatment center, except for optional workplace visits. Relapse prevention is part of regular treatment and is addressed during group treatment, individual counseling, or through specific assignments (eg, composing a relapse prevention plan).

#### Enhanced Treatment

In addition to the regular treatment condition, patients in the enhanced treatment condition will be provided access to the AGRIPPA app that is available on the Android and iOS operating systems for mobile devices. The app consists of three components: two behavioral strategies and an education module. “Insight Cards” and “Value-Based Goals” are specific behavior regulation strategies that have been derived from the SOLACE study and aim to prevent relapse. In addition, an information and education module has been developed in response to patient and health care provider preferences that were expressed during the app design phase.

##### Component 1: Insight Cards

Patients can use “Insight Cards” to document any personally meaningful experience, thought, or idea that relates to their treatment or corresponding personal development. The main aim is that these “insights” remain accessible after treatment and thereby support the transfer of key treatment principles to each patient’s personal context. When capturing an insight, patients first type a title and a short description. Subsequently, they have the possibility to assign a corresponding value and a related picture to the insight (see Figure 1). When patients routinely save their experiences in the app during their treatment period, this will result in a chronologic overview of key experiences over time. During treatment, health care providers will be able to discuss this content with patients to check whether the treatment was received as intended. For patients, the app provides a means to reflect on important experiences during and after treatment. The app also enables patients to mark specific experiences as “favorite” and to share their Insight Cards via email or WhatsApp with their relevant others. After treatment, patients have continuous access to their personal collection of Insight Cards to recover specific insights, to explain specific insights of their condition or treatment to other people, or to reflect on their experiences. Moreover, they can add new Insight Cards to their collection after treatment completion if they have experienced relevant events or insights.

**Figure 1 figure1:**
[figure not shown]
Three screenshots from the AGRIPPA app. Left: example of an insight card, including a related photo, title, two associated values, and description. Middle: Overview of a fictitious goal to go for a hike, including three steps and a related insight. Right: Overview screen of the education and information module. The first row includes treatment-specific exercises, the second row includes general information about the app, and the third row includes links to other support materials.

##### Component 2: Value-Based Goals

The Value-Based Goals module facilitates the formulation of meaningful goals (eg, going for a hike with friends on Saturday morning to be sociable) and subsequent action planning of each consecutive step toward this goal. The procedure is divided into four steps. First, patients formulate their overall goal. Second, patients reflect on desirability, self-efficacy, estimated time to achievement, and social support concerning this goal. Third, patients formulate a corresponding higher-order value (eg, values such as loyalty, friendship, or adventurousness in relation to a goal of going hiking with old classmates), and, optionally, a reward once the goal has been achieved. In the final part, patients can plan multiple “steps,” comprising single or recurrent activities that need to be performed to achieve the corresponding goal (eg, buying hiking shoes or planning a weekly training session). For each step, patients plan where and when the specific activity will be performed. They can also add reminders or schedule each step in their mobile calendar. In the final part of the step-planning sequence, patients reflect on potential barriers and formulate coping strategies in anticipation of these barriers (eg, preparing dinner in advance to avoid missing a training session). If a goal has been achieved, patients can directly create an Insight Card of this particular experience. Figure 1 (middle) shows an overview of steps within a specific goal.

##### Component 3: Information and Education

By default, the Information and Education module includes general information about the AGRIPPA project and instructions on how to use both strategies. In addition, each treatment center can add specific content to this section, including information materials, website links, figures, embedded videos, and assignments. The main reason for including this module is to create a single environment for all supplementary materials of the treatment program. Figure 1 (right) depicts the main screen of this module.

#### Modifications

During the training session, we recommend health care providers to regularly discuss the app during treatment. However, due to expected variations in digital literacy and other urgent topics, health care providers are allowed to modify the intensity according to their clinical judgement.

#### Adherence to the Intervention Protocol

The app will be made available to the members of the treatment teams to become accustomed to the content. The training will be provided by two researchers ([name]) and include an overview of the purpose and rationale of the study, as well as detailed instructions on how to use the app within the context of the treatment program. This includes identifying an appropriate moment within the treatment program to introduce the app, determining which member of the team will be responsible for the introduction and encouragement to regularly evaluate the app content, and provide feedback to the participant. During the study, a researcher will have biweekly contact with the treatment team to obtain feedback and discuss progress. Furthermore, two audit sessions will be planned at each location. The researcher will schedule an appointment to discuss overall progress, protocol adherence, and to share examples of good practice with the treatment team. During these sessions, the researcher will also inquire about substantial deviations from the protocol or discontinuation of the app during treatment.

#### Concomitant Care

During the treatment program, patients are not allowed to be treated elsewhere for their chronic pain unless the treatment team decides to refer the patient for a specific reason.

### Outcomes

All six treatment facilities routinely collect outcome data with an electronic survey to monitor their patients [33]. All demographics, baseline measurements, as well as the primary outcome will be obtained by this procedure. Any outcome measures that are not part of the routine assessment will be obtained through an additional electronic survey. Table 1 includes an overview of all outcome domains, measures, and planned analysis methods. The participant flow that is depicted in Figure 2 includes all time points of data collection in this study. A researcher who is not involved with the treatment program will monitor all incoming data and will promote study retention using email reminders after 7 days and telephone reminders at 15 and 21 days postmeasurement.

**Table 1 table1:** Planned outcome domains, outcome measures, and statistical methods.

Outcome		Hypothesis/research question	Outcome measure	Method of analysis
**Primary**				
	Self-perceived pain disability	The development of pain disability over time after IMPT^a^ will be more favorable for the enhanced treatment condition compared to usual care.	PDI^b,c^	Multilevel analysis
	Planned subgroup analysis on patients that scored 1 (“very much better”) or 2 (“much better”) on the GPE^d^ scale at *t*_1_^e^.	For patients that experienced meaningful treatment success, the development of pain disability over time after IMPT will be more favorable for the enhanced treatment condition compared to usual care.	1. PDI^c^ 2. GPE^f^	Multilevel analysis

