## Methods

### Design

We will perform a randomized controlled multicenter superiority trial with two parallel groups in the Netherlands. Both groups will receive standard IMPT, but the experimental group will be provided with the AGRIPPA app that they can access both during and after the treatment program. The nature of the intervention does not allow for masking the condition for health care providers or patients. The allocation ratio will be 1:1.

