##### Global Perceived Effect

The global perceived effect (GPE) evaluates to what extent the patient’s current condition has improved or worsened compared to the period prior to the treatment program. Patients respond with a 5-point Likert scale, ranging from 1 (very much improved) to 5 (very much worsened). The psychometric properties of this questionnaire have been tested in the context of various musculoskeletal disorders and are considered adequate [50].

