### Data Analysis

During all analyses, the treatment condition will be masked to the researchers. We will analyze the data according to the intention-to-treat principle and include patients in the analysis regardless of their adherence to the treatment protocol. We will perform no interim analysis. We will collect data at the following time points: –t_1_ (baseline), t_1_ (immediately postintervention), t_2_ (3 months postintervention), t_3_ (6 months postintervention), and t_4_ (12 months postintervention). Prior to the main analysis, we will check the randomization by examining the distribution of baseline characteristics between both groups.

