#### Primary Analysis: Pain Disability

In our primary analysis, we will test the difference in the development of pain disability over time between patients in the enhanced condition and patients in the treatment condition. To account for the assumed dependence of the repeated observations and treatment locations, we will perform a multilevel analysis. In our hierarchical model, time points (level 1) will be nested in patients (level 2) and patients nested in treatment locations (level 3). Our main analysis will include the effects of time, treatment condition, treatment location, and the interaction between time and treatment condition, with a random intercept for patients. In addition, the model will be adjusted for sex, age, pain intensity, and pain duration. In the case of a significant 2-way interaction between time and treatment condition, posthoc contrasts between the treatment conditions at 3, 6, and 12 months will be calculated. We will also perform a subgroup analysis for patients that report a positive treatment effect at t_1_ (ie, a GPE score of 1 or 2).

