### Participant Timeline

Patient eligibility screening, informed consent, and treatment allocation procedures, as well as the baseline assessment, will be completed prior to the start of the treatment program. Patients in the enhanced treatment condition will receive instruction on how to download and use the app, and both strategies will be explained by a member of the treatment staff. To match the existing treatment content and procedures, the moment that the app will be introduced to patients can vary between locations. During the treatment phase, the app is considered a supplement to the main treatment activities and patients are free to decide how and when to use the app. Health care providers will be instructed to encourage and facilitate using the strategies when they expect it will reinforce the treatment process. However, both strategies can largely be used independently of any treatment activity and are expected to minimally affect direct treatment time. A member of the research team will be available to the treatment staff throughout the experimental phase for additional questions, support, and discussions regarding optimal use. Following treatment, there will be no additional monitoring in the enhanced treatment condition. Patients will continue to be able to use the app at their discretion. Posttreatment data will be obtained directly posttreatment (t1), and at 3 months (t2), 6 months (t3), and 12 months (t4) posttreatment.

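### The planned between-arm comparison among patients who rate themselves improved at t1 selects on a response given after randomisation and after app use, so it cannot carry a causal superiority hypothesis

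*Protocol article*

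**What the plan says.** The subgroup appears twice in the protocol article. In Table 1 it is the second row under the Primary heading ("Planned subgroup analysis on patients that scored 1" or 2 on the GPE at t1). It has its own directional hypothesis ("For patients that experienced meaningful treatment success, the development of pain disability over time after IMPT will be more favorable" for the enhanced arm than for usual care), to be tested by multilevel analysis of the PDI. The section Primary Analysis: Pain Disability repeats it after the main model: a "subgroup analysis for patients that report a positive treatment effect at t_1_ (ie, a GPE score of 1 or 2").

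Four other statements fix the order of events:

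- Participant Timeline: "treatment allocation procedures, as well as the baseline assessment, will be completed prior to the start of the treatment program".
- Design: "the experimental group will be provided with the AGRIPPA app that they can access both during and after the treatment program". The same section says that neither patients nor providers can be masked.
- Data Analysis: the selection time point is "t_1_ (immediately postintervention").
- Global Perceived Effect: the patient rates whether the "current condition has improved or worsened compared to the period prior to the treatment program".

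Data Analysis also commits the analyses to intention to treat. The article does not call the subgroup exploratory, and Strengths and Limitations does not mention it.

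**The concern.** The GPE at t1 is an outcome, not a baseline characteristic. It rates change over a period in which one arm had the app and the other did not, and the raters know their arm. The app could alter the rating by helping during treatment, or simply because an unmasked patient who was given something extra feels more improved. The authors concede in Strengths and Limitations that a placebo effect of receiving an app is not controlled.

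If the app moves some patients into GPE 1-2, the enhanced-arm subgroup includes patients whose counterparts under usual care would have scored 3 or worse and been left out. The two subgroups then differ in prognosis before the app has done anything to later disability.

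The aim of the trial is to maintain gains after successful treatment, so a result confined to the successfully treated is easy to read as the direct answer. As planned, it would be reported with a superiority hypothesis and a primary-outcome label that the selection cannot support.

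**Working it through.** **1. Order of events.** Allocation comes before the programme (Participant Timeline). App access runs during the programme (Design). The GPE at t1 follows the programme (Data Analysis) and rates change since before it (Global Perceived Effect). The selection variable is therefore measured after randomisation and after exposure. This step settles the structural point and needs no figures.

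**2. Inputs for the size.** The article gives no PDI standard deviation, no GPE 1-2 share and no correlation between GPE and later PDI. All of these are assumed below. The article does supply 1:1 allocation, a minimum of 157 participants, 20% attrition, and a clinically important PDI change of 8.5 to 9.5 points. It states no sample size or power for the subgroup.

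**3. Model.** Treat GPE as a cut on a standard normal scale, with a share p rating 1 or 2. The mean latent score among those selected is λ(p) = φ(Φ⁻¹(p))/p:

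| p | 0.40 | 0.45 | 0.50 | 0.55 | 0.60 | 0.70 |
|---|---|---|---|---|---|---|
| λ(p) | 0.966 | 0.880 | 0.798 | 0.720 | 0.644 | 0.497 |

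Suppose that the app raises the share from p₀ to p₁ and has no effect on PDI. The spurious subgroup difference against the app is then [λ(p₀) − λ(p₁)] × ρ × SD, where ρ is the strength of the association between latent GPE and the PDI measure.

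**4. Later PDI level, SD 13, ρ 0.4 to 0.6.**

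- 50% to 55%: 0.078 × (0.4 to 0.6) × 13 = 0.4 to 0.6 points
- 50% to 60%: 0.154 × (0.4 to 0.6) × 13 = 0.8 to 1.2 points
- 50% to 70%: 0.301 × (0.4 to 0.6) × 13 = 1.6 to 2.4 points
- 40% to 50%: 0.168 × (0.4 to 0.6) × 13 = 0.9 to 1.3 points
- 40% to 60%: 0.322 × (0.4 to 0.6) × 13 = 1.7 to 2.5 points

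**5. PDI change after t1, SD 14.** Here an unmeasured prognostic factor correlates 0.3 to 0.5 with both GPE and PDI change, so ρ is the square of that, 0.09 to 0.25.

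- 40% to 45%: 0.086 × (0.09 to 0.25) × 14 = 0.1 to 0.3 points
- 40% to 50%: 0.168 × (0.09 to 0.25) × 14 = 0.2 to 0.6 points
- 40% to 60%: 0.322 × (0.09 to 0.25) × 14 = 0.4 to 1.1 points

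A simulation of this second model, with control shares of 40% to 70%, agrees. It gives 0.2 to 0.6 points for a 10-point rise, 0.3 to 1.1 for a 20-point rise, and about zero when the share does not change. The all-randomised comparison stays at about zero throughout.

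**6. Error rate.** Patients expected per arm after attrition: 157 × 0.8 / 2 = 62.8. With shares from 40% to 90%, the subgroup has about 25 to 56 patients per arm. At those sizes, in the second model, the nominal 5% error rate rises to at most about 6.7%.

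**The case against.** **Status.** The row is labelled a planned subgroup, Table 1 groups its rows by outcome, and the analysis section adds the subgroup only after the primary model ("We will also perform a subgroup analysis for patients that report a positive treatment effect"). The three hypotheses in Study Objectives do not include it, and the first of them, on maintenance of improvement, is tested in all randomised patients. This stands. A reader might infer that the trial's primary conclusion is compromised. The documents do not support that, because the main model uses everyone randomised.

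**Certainty.** A reader might also infer that the subgroup result must be biased. It need not be: the bias is near zero if the app leaves membership alone, and adjustment for sex, age, pain intensity and pain duration may remove part of any imbalance. This too stands, but it does not restore the hypothesis. Adjustment reaches only measured factors, and equal GPE shares in the two arms would not prove that the same kinds of patients were selected.

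**Size.** All the illustrated biases are well below the 8.5 to 9.5 point important change, and the largest needs a 20-point rise in share with a correlation of 0.6. This stands. Nor can it be said that half the sample is lost, since the article gives no responder share.

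**Replacement endpoint.** One tempting substitute, in all randomised patients, is sustained success: GPE 1-2 at t1 and PDI at t4 not worse than at t1 by 8.5 points or more. It puts the same unmasked rating into the endpoint. Assume a t1-to-t4 PDI change with mean 0 and SD 14, uncorrelated with GPE. The PDI part is then met with probability Φ(8.5/14) = 0.728. A 10-point rise in GPE share with no PDI effect gives 10 × 0.728 = 7.3 percentage points of spurious benefit for the app, and a 20-point rise gives 14.6. Correlations up to 0.5 change these little (7 to 8, and 14 to 15). It also merges reaching success with keeping it.

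**Conclusion.** The point holds as one of labelling and inference for a supporting analysis. Membership of the GPE 1-2 subgroup is settled after randomisation, by unmasked patients, in a period when only one arm has the app. A between-arm PDI difference within it can be read as a causal app effect only on the further assumption that the app does not alter the make-up of that group. The article neither states nor defends this assumption.

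Under the assumed inputs, a rise in share of 5 to 20 points with no PDI effect produces about 0.1 to 2.5 PDI points against the app. A fall in share reverses the sign. If the app also truly improves response at t1, the bias could go either way. These figures show a plausible order of magnitude and are not estimates for this trial.

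**What to change.** - Move the subgroup row out of the Primary block of Table 1. There and in Primary Analysis: Pain Disability, label it exploratory and non-causal.
- Remove the hypothesis that the enhanced arm will do better within this subgroup.
- Report the proportion with GPE 1-2 at t1 by arm beside the result. Say that unequal proportions signal selection, and that equal ones do not rule it out.
- State that the conclusion on maintenance of gains rests on the PDI comparison in all randomised patients, which is already planned.
- Do not substitute the GPE-based sustained-success composite.

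The cost is a few lines of wording and one extra table row from data already being collected. Sample size, visits and the main model do not change.

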**Secondary (quality of life)**				
	Health care costs	The enhanced treatment condition will be cost-effective compared with usual care at 3 and 6 months posttreatment.	1. SF-12^f,g^ 2. iPCQ^f,h^	Cost-effectiveness analysis
	Illness perception	The development of illness perceptions over time after IMPT will be more favorable for the enhanced treatment condition compared to usual care.	IPQ-K DLV^c,i^	Multilevel analysis
	Pain self-efficacy	The development of pain self-efficacy over time after IMPT will be more favorable for the enhanced treatment condition compared to usual care.	PSEQ^c,j^	Multilevel analysis
	Pain intensity	The development of outcome measures over time may be affected by the level of pain intensity	NRS^c,k^	Multilevel analysis
**Engagement and usability**				
	Overall engagement	The level of engagement and usability will be positively associated with a change in pain disability during follow up (*t*_4_^l^ – *t*_1_).	1. System usability scale^f^ 2. System usage data of AGRIPPA app (see below)	Multiple linear regression
	Frequency of engagement	How does the frequency of engagement vary over time after treatment?	Average number of logins per week	Descriptive statistics
	Depth of engagement	How does the average number of features accessed per login vary after treatment?	Average number of features accessed per log-in	Descriptive statistics
	Duration of engagement	How do the average minutes spent at each login as well as the total time spent with the app per week vary after treatment?	1. Average minutes spent at each login. 2. Total time spent with the app	Descriptive statistics
	Active engagement with Insight Cards	To what extent will the number of created Insight Cards increase or decrease after treatment?	Number of Insight Cards created	Descriptive statistics
	Active engagement with VBG^m^	To what extent will the number of created VBG cards increase or decrease after treatment?	1. Number of VBGs created. 2. Number of steps created	Descriptive statistics

^a^IMPT: interdisciplinary multimodal pain therapy.

^b^PDI: Pain Disability Index.

^c^Outcome measure is part of routine care.

^d^GPE: global perceived effect.

^e^*t_1_*: immediately postintervention.

^f^Outcome measures will be obtained with an additional electronic survey.

^g^SF-12: 12-item short-form health survey.

^h^iPCQ: iMTA Productivity Cost Questionnaire.

^i^IPQ-K DLV: Dutch language version of the Illness Perception Questionnaire.

^j^PSEQ: Pain Self-Efficacy Questionnaire.

^k^NRS: numeric rating scale.

^l^*t_4_*: 12 months postintervention.

^m^VBG: Value-Based Goals.

